### Statistical Analysis

All analyses will be performed using SPSS (version 25.0; IBM Corp). Continuous variables will be checked for normality using visual inspection (histograms and Q-Q plots) and the Shapiro-Wilk test. Descriptive statistics will be reported as means and SDs for normally distributed variables or medians and IQRs for nonnormal variables. Categorical variables will be reported as counts and percentages. The details are presented in Textbox 2.

Detailed statistical analysis plan.
**Demographics**
Amputee (group 1) and control (group 2) demographics will be compared. Normally distributed continuous variables will be assessed using an independent samples t test, nonnormal continuous variables will be assessed using the Mann-Whitney U test, and categorical variables will be assessed using the chi-square or Fisher exact test.
**Motor imagery (MI) variables**
Measures will include the Movement Imagery Questionnaire-3, including its subscales: kinesthetic MI, internal MI, external MI, and total score as well as the Orientate app accuracy and completion time, and motor execution time–MI time for the dominant and nondominant hand.Comparisons will be performed using the analysis of covariance, adjusting for age, dominance, and residual limb length.If the analysis of covariance assumptions are not met, nonparametric alternatives will be applied.

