## Methods

### Participants

The required sample size for the study was determined using G*Power software (version 3.1; Heinrich Heine University Düsseldorf). The calculation was based on the Movement Imagery Questionnaire-3 (MIQ-3) scores reported by Saimpont et al [27], which served as a reference for the primary outcome of this study.

Although Saimpont et al [27] reported a large effect size (Cohen *d*=1.41) in a healthy population, a more conservative estimate (Cohen *d*=0.8) was applied in this study’s power analysis to better reflect expected variability among participants who underwent transradial amputation. Using a 2-tailed independent samples *t* test, with an α of .05 and power (1–β) of .80, the required total sample size was calculated as 30 participants (n=15, 50% per group).

This sample size provides sufficient statistical power to detect large effects (Cohen *d*≥0.8) between groups while also allowing for potential participant dropouts. A sensitivity analysis showed that detecting moderate effects (Cohen *d*=0.6) would require approximately 18 participants to achieve equivalent power; however, as the study primarily aims to detect large between-group differences, the planned sample of 30 participants (n=15, 50% per group) was considered adequate.

Participants will be recruited from prosthetics and orthotics centers located in Istanbul, Turkey. The study group will consist of volunteers who meet the inclusion criteria; therefore, no probabilistic sampling method will be used. Inclusion criteria for the amputee and control groups are listed in Textbox 1.

Inclusion criteria for the amputee and control groups.

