### Outcome Measures

According to the study hypothesis, the primary outcome is MIA assessed using the MIQ-3, which was selected as the primary end point given its central role in prosthetic motor control, motor learning, and functional adaptation in individuals who have undergone transradial amputation.

The secondary outcomes include the following:

Upper-limb functional performance, assessed using the Box and Block Test (BBT), Jebsen-Taylor Hand Function Test (JTHFT), and the Disabilities of the Arm, Shoulder, and Hand (QuickDASH) questionnaireMI performance indicators, including the Mental Chronometry Test (MCT) and hand mental rotation task, as secondary measures of MIAProprioceptive and sensorimotor accuracy, measured by joint position sense (JPS) error using a validated digital goniometer app (DrGoniometer [CDM SrL])General balance and flexibility, evaluated by the Functional Reach Test (FRT) as an indicator of overall functional stabilityCognitive and psychological screening, including the Standardized Mini-Mental State Examination (SMMSE), Beck Depression Inventory (BDI), and Visual Analog Scale (VAS) for pain intensity

Each participant will be assessed once, as this is a cross-sectional study with no intervention. To minimize potential bias, all assessments will be performed by trained evaluators following standardized protocols. Participants will be recruited according to predefined eligibility criteria to reduce selection bias, and data will be systematically recorded to prevent information bias. As no intervention is applied, performance bias is not applicable.

To minimize the risk of type I error resulting from multiple comparisons, the Bonferroni correction will be applied to secondary outcome analyses.

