### MIQ-3 Description

The MIQ-3, originally developed by Williams et al [31], will be used to assess imagery ability in all individuals included in the amputee and control groups. The Turkish validity and reliability study of this questionnaire was conducted by Dilek et al [32]. The MIQ-3 consists of 12 items and evaluates internal visual imagery, external visual imagery, and kinesthetic imagery abilities through 4 actions for each domain. These actions include leg raising, jumping, shoulder flexion, and forward bending. The movements are designed to assess MI capacity in internal, external, and kinesthetic dimensions.

Participants will initially perform each movement physically. They will then be asked to mentally perform the same movements as a cognitive task. This mental imagery task will be rated using a 7-point Likert-type scale (1=very hard to see or feel and 7=very easy to see or feel). For scoring, the average score of the 4 movements corresponding to each subdimension will be calculated.

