**Missing data, outliers, and multiple comparisons**
Missing data will undergo listwise deletion.Trials with outlier values exceeding 2 SDs from the group mean will be excluded. Sensitivity analyses with and without outliers will be performed.The Bonferroni correction will be applied for multiple comparisons.

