**Significance**
All tests will be 2-tailed, with *P*<.05 considered statistically significant.

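### No single MIQ-3 score is named as primary, and the two Bonferroni statements leave it open whether the four MIQ-3 tests are corrected, so the error rate of the primary claim is not fixed

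*Protocol article*

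**What the plan says.** Under Outcome Measures, the article states that "the primary outcome is MIA assessed using the MIQ-3". It does not say which MIQ-3 score. The same section closes by promising that "the Bonferroni correction will be applied to secondary outcome analyses".

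MIQ-3 Description defines three subscales (internal visual, external visual, kinesthetic) and one scoring rule: "For scoring, the average score of the 4 movements corresponding to each subdimension will be calculated". It gives no rule for a total.

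Textbox 2, which the article presents as its detailed statistical analysis plan, lists the MIQ-3 among the motor imagery variables to be compared between groups, "including its subscales: kinesthetic MI, internal MI, external MI, and total score". That makes four scores, in no order of priority. They stand next to the Orientate and chronometry measures, which Outcome Measures classes as secondary.

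The multiplicity entry of the same textbox says: "The Bonferroni correction will be applied for multiple comparisons". It gives neither a family nor a divisor and is not limited to secondary outcomes. The Significance entry says "All tests will be 2-tailed" and sets the threshold at .05.

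Participants sizes the study for a single two-tailed independent-samples t test "with an α of .05 and power (1–β) of .80", at d=0.8, with 15 per group.

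**The concern.** The design rests on one test at .05, but the analysis produces four MIQ-3 tests that could each be reported as the primary result. Nothing in the article says which one decides the question, or whether they share an alpha of .05.

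Two things follow. First, the primary score could be chosen after the results are seen. This matters more here than usual, because a single unblinded researcher, who is an author, does all the assessments (Study Design and JPS Description). Second, the two Bonferroni sentences lead to different thresholds, .05 or .0125 per score, and so to different error rates and different power for the only outcome with a stated power.

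**Working it through.** **Inputs from the article.** 15 per group; d=0.8; two-sided alpha .05; power .80 (Participants). Four MIQ-3 scores compared (Textbox 2).

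**Inputs assumed.** The article gives no correlation between subscales. I took a common correlation rho from 0 to 0.9, equal variances, normal scores, and the total as the mean of the three subscales.

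**Step 1: the plan's own figure.** For a two-sample t test the noncentrality is d × √(n/2) = 0.8 × √7.5 = 2.19 on 28 df. The two-sided .05 critical value is 2.048, which gives power of 56%, not 80%. Reaching 80% takes 25.5, so 26 per group (52 in total). The stated 30 does not follow from its inputs. That is a separate error; here it only means that the single-test baseline is 56%.

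**Step 2: error rate if the four scores are each tested at .05 and any one counts.** Four independent tests would give 1 − 0.95⁴ = 18.5%, but the total is built from the subscales, so the true rate is lower. I used simulation under no true difference: 15 per group, 100,000 replicates per rho. The last column tests each score at .05/4 = .0125.

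| rho | any of 4 at P<.05 | any of 4 at P<.0125 |
|---|---|---|
| 0 | 16.4% | 4.5% |
| 0.2 | 15.2% | 4.3% |
| 0.3 | 14.4% | 4.0% |
| 0.5 | 12.8% | 3.5% |
| 0.7 | 11.2% | 3.1% |
| 0.8 | 10.1% | 2.8% |
| 0.9 | 8.4% | 2.3% |

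These are t tests. Repeating the .05 column as ANCOVA with three covariates (25 df), closer to the planned analysis, changes it by about 0.3 points at most.

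**Step 3: power if Bonferroni covers the four scores.** At .0125 the critical value on 28 df is 2.669. With noncentrality 2.19, power per score is 33%, against 56% at .05. Reaching 80% at .0125 takes 36.4, so 37 per group.

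**Step 4: one designated score.** The error rate is 5% by construction, with no multiplicity cost to the primary test.

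**The case against.** The strongest reply is that the plan already corrects for multiplicity. The textbox sentence on Bonferroni is unrestricted, and the promise under Outcome Measures to correct secondary analyses does not say that primary ones are exempt. Read together, the four MIQ-3 tests could be covered, and the familywise error would then be below 5%. This stands in part. A reader might infer that Bonferroni is reserved for secondary outcomes; the textbox does not support that. But it names no family or divisor, so it does not settle the matter the other way either.

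A reader might also infer that the plan carries a familywise error of 11-15% instead of 5%. The article does not support that as a property of the plan. The figure needs uncorrected tests, a rule that any one of four scores suffices (no success rule is stated), and subscale correlations of about 0.2 to 0.7, which are assumed.

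It can be said too that the missing total-score rule is minor, since the questionnaire is published and an article may leave routine scoring to its source. That is fair for the rule alone. It matters only if the total becomes the primary end point.

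Nor is the total the obvious choice: the Introduction gives kinesthetic imagery a key role in prosthetic control. I agree, and the point does not depend on which score is chosen.

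**Conclusion.** The concern holds in this form: the primary MIQ-3 score is not designated, and the two statements on Bonferroni differ in scope, so the familywise error of the primary claim is not fixed. It is about 8-16% if the tests are uncorrected and any one score counts, and 2.3-4.5% if each is tested at .0125. Both ranges rest on assumed equal correlations from 0 to 0.9. The .0125 threshold also assumes that the Bonferroni family is exactly these four scores.

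The corrected reading has its own cost: power at d=0.8 is 33% instead of 56%. Both are t test figures, and the shortfall from 80% to 56% must not be attributed to multiplicity.

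This is not detail left to an unseen document, because it rests on what the article's own outcome section and analysis textbox state. It should be changed, and doing so is nearly free.

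**What to change.** Before any group comparison is run:

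- Name one MIQ-3 score as the single primary end point, tested at two-sided .05. The total would serve as an example, with its scoring written into MIQ-3 Description; a subscale would also do.
- Move the other three MIQ-3 scores to the Bonferroni-corrected secondary family.
- Reword the Bonferroni sentence in Textbox 2 to match Outcome Measures, stating the family it covers.

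The alternative, Bonferroni over all four scores as co-primary, would need 37 per group for 80% power at d=0.8, so it does not fit the planned 15.

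The cost is a few sentences and no new data. The downside is that an effect seen only in a non-primary score becomes a secondary finding. A reader might infer that, because no analyses have been run, the choice is still free of bias. The Results section does not support that much: data from 16 of the 30 participants are already entered, cleaning has begun, and assessment is unblinded. The article should therefore say that the score was chosen after data entry had started but before analysis.

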**Methods:**

This cross-sectional study will include 15 individuals who have undergone transradial amputation (aged 18-65 y) and 15 age- and sex-matched healthy controls, recruited from prosthetics and orthotics centers in Istanbul, Turkey. Assessments will include MIA, hand mental rotation, upper extremity function, and proprioception. MIA will be measured using the Movement Imagery Questionnaire-3 and the Mental Chronometry Test. Hand mental rotation ability will be assessed via the Orientate mobile app. Upper extremity function will be evaluated using the Box and Block Test; Jebsen-Taylor Hand Function Test; and the Quick Disabilities of the Arm, Shoulder, and Hand questionnaire. Proprioception will be assessed through joint position sense measurements. All data will undergo appropriate statistical analyses.

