### Study Design

This study is registered in the ClinicalTrials.gov database (NCT06541379) and uses a cross-sectional design with multicenter recruitment and single-center assessment. Participants will be recruited from several prosthetics and orthotics clinics located in Istanbul, Turkey, while all evaluations will be conducted at the prosthetics and orthotics research and application center of Istanbul Medipol University. All necessary institutional approvals were obtained before study initiation.

A total of 30 participants will be included: 15 (50%) individuals with unilateral transradial amputation who use a myoelectric prosthesis and 15 (50%) healthy control participants matched for age and sex. The study flowchart describing the recruitment and assessment process is presented in Figure 1.

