All measurements will be conducted using the validated digital goniometer app DrGoniometer [40,41], which has demonstrated high validity and reliability for upper-limb joint measurements, including forearm supination and elbow flexion [40,41], although it has not been specifically validated in populations who have undergone amputation. Correctness (+5° and –5°) and reaction-time metrics are predefined. Absolute error, constant error, and variable error will be calculated to quantify accuracy and consistency. Due to the nature of the assessments, assessor blinding was not feasible; however, all measurements were conducted using a standardized protocol with fixed positioning and predefined verbal instructions to minimize bias

Covariates such as age, sex, amputation level, prosthesis experience, and tested side will be recorded and adjusted for in the statistical analyses.

All assessments will be completed within approximately 90 minutes, including short breaks as needed, in the following standardized order: MIQ-3, MCT, JTHFT, QuickDASH questionnaire, FRT, and finally JPS.

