**MI and proprioception**
Correlations between MI and proprioception measures (elbow 30°, 60°, and 90°, and shoulder 90° flexion and abduction) will be conducted.Regression models will evaluate predictors of proprioceptive performance, with covariates age, dominance, and residual limb length.

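### Controls are matched on age and sex, but the group-comparison model omits sex, and the section that says sex is adjusted for contradicts the covariate lists in Textbox 2

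*Protocol article*

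**What the plan says.** The Study Design section plans "15 (50%) healthy control participants matched for age and sex", and the abstract's Methods paragraph says the same ("15 age- and sex-matched healthy controls"). Neither states whether matching is person to person or by group frequency.

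Textbox 2, under Motor imagery (MI) variables, gives the only amputee-versus-control model for the imagery outcomes. Outcome Measures names one of these, the MIQ-3, as primary. The model reads: "Comparisons will be performed using the analysis of covariance, adjusting for age, dominance, and residual limb length". The regressions of function on imagery (MI and upper limb function) carry the same three covariates, and so do those for joint position sense: "Regression models will evaluate predictors of proprioceptive performance, with covariates age, dominance, and residual limb length".

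The JPS Description closes with a different list: "Covariates such as age, sex, amputation level, prosthesis experience, and tested side will be recorded and adjusted for in the statistical analyses".

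On losses, Textbox 2 says "Missing data will undergo listwise deletion", and the Participants section says the sample size was set "while also allowing for potential participant dropouts", without a rate.

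**The concern.** Two things are wrong. First, an analyst cannot follow both covariate lists. Sex is adjusted for in one and absent from the other, and age is the only variable named in both. With 30 people, a covariate set chosen after the data are seen could move the primary result.

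Second, a factor used to balance the groups by design should normally be in the model that compares them. If it is left out, the variance that matching removed from the group difference is still counted in the residual. The standard error is then too large, and precision that the matching should have bought is lost. If exclusions later unbalance sex, the model has no term to correct it.

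**Working it through.** **Covariate lists side by side**

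| Place | Age | Sex | Other covariates |
|---|---|---|---|
| Matching (Study Design; abstract) | yes | yes | none |
| JPS Description | yes | yes | amputation level, prosthesis experience, tested side |
| Textbox 2, MI variables | yes | no | dominance, residual limb length |
| Textbox 2, MI and upper limb function | yes | no | dominance, residual limb length |
| Textbox 2, MI and proprioception | yes | no | dominance, residual limb length |

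The JPS Description and the proprioception regressions concern the same outcome, so their conflict is direct. The conflict with the MI model rests on the general reference to the statistical analyses in the JPS sentence.

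**Inputs.** 15 per group and two-sided 5% tests come from the document. The plan gives no sex split, sex effect or dropout rate and no figure of its own on this point. Assumed here: 10 men and 5 women in each group, and a sex effect g of 0.2 to 1.0 residual SD.

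**Match intact: standard error.** Sex is balanced, so it cancels from the group difference and there is no bias. Left out of the model, it adds 2 × 15 × (10/15) × (5/15) × g² = 6.67g² to the residual sum of squares on 28 degrees of freedom. The expected residual variance is therefore 1 + 0.238g², and the standard error is inflated by √(1 + 0.238g²):

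- g = 0.2: √1.0095 = 1.005, about 0.5%
- g = 0.5: √1.0595 = 1.029, about 3%
- g = 0.8: √1.152 = 1.073, about 7%
- g = 1.0: √1.238 = 1.113, about 11%

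Simulation with age in both models agrees. The mean standard error is 0.364, 0.373 and 0.388 without sex (g = 0.2, 0.5, 0.8) against 0.362 with it.

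**Match intact: type I error.** The numerator keeps its true variance, while the denominator is a noncentral chi-square with 28 degrees of freedom and noncentrality 6.67g². Integrating the two-sided rejection probability over that distribution gives 4.9%, 4.4%, 3.6% and 3.0% for g = 0.2, 0.5, 0.8 and 1.0. A simulation of 200,000 data sets per scenario, with age in the model, gives 4.9%, 4.4%, 3.7% and 3.0%, against 4.9% to 5.0% with sex included. Smaller simulations give 4.7%, 4.2%, 3.5% and 2.9%; the differences are simulation error.

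**Match intact: power.** At a true difference of 0.8 SD, simulated power is 55.3%, 53.8% and 50.2% without sex (g = 0.2, 0.5, 0.8) and 55.9% with it. Precision is scarce in any case: the independent t test named under Participants has about 56% power with 15 per group at d = 0.8. That is a separate matter.

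**Match broken by deletions.** If k of the 5 women are lost from one group and nobody else is lost, the unadjusted difference shifts by g × [5/15 − (5 − k)/(15 − k)]:

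- k = 1: 0.048g, or 0.01 to 0.04 SD for g = 0.2 to 0.8
- k = 2: 0.103g, or 0.02 to 0.08 SD
- k = 3: 0.167g, or 0.03 to 0.13 SD

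With two women lost, simulated bias is about 0.02, 0.05 and 0.08 SD without sex in the model and about zero with it. The largest case, 0.13 SD, compares with a standard error of √(1/12 + 1/15) = 0.39 SD, so it is about a third of one standard error. If two of the 15 are lost at random, the chance that both are women is (5 × 4)/(15 × 14) = 20/210, about 10%.

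**The case against.** The covariate sentence with sex in it closes the joint position sense section and includes tested side, which suits a joint-angle test better than a questionnaire. It may not have been meant for the MIQ-3. This stands in part: the conflict is sharpest with the proprioception regressions and less certain for the imagery model. But the wording is general, and sex is a matching factor missing from the imagery model however that sentence is read.

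A reader might infer more than the documents support:

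- **That the primary estimate is biased.** It is not while the match holds. Bias needs sex-selective losses, and each participant is assessed once, in about 90 minutes, with no intervention. The Results section reports that all 16 people recruited so far completed every assessment.
- **That the analysis ignores the matching altogether.** Age, the other matching factor, is in the model.
- **That broken pairs need a rule, or that a paired analysis is required.** Individual pairing is never stated, and the model is already unpaired, so listwise deletion removes only the incomplete person.

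The sizes also rest on assumed sex effects. At 0.2 SD the loss is negligible.

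The point cannot be set aside as detail left to a fuller plan. Textbox 2 is presented as the detailed analysis plan, and it fixes the lists. It is also true that residual limb length is recorded only for amputees (Demographic Information), so the group model has a further difficulty that adding sex does not solve. That needs its own correction.

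**Conclusion.** The point holds as an inconsistency with a modest cost in precision. The covariate lists contradict each other, and the primary amputee-versus-control model leaves out one of the two matching factors. With the match intact the consequence is conservatism, not bias: standard errors about 0.5% to 11% too large and a type I error between just under 5% and about 3%, for assumed sex effects of 0.2 to 1.0 SD and a 10-to-5 sex split. Bias of roughly 0.01 to 0.13 SD could arise if deletions removed one to three of five women from one group only, with sex effects of 0.2 to 0.8 SD. That is possible but unlikely in this design. The change is worth making because it touches the primary comparison and costs almost nothing.

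**What to change.** Add sex, alongside age, to every amputee-versus-control model under Motor imagery (MI) variables in Textbox 2. Make the JPS Description and the three Textbox 2 entries (MI variables, MI and upper limb function, MI and proprioception) give one covariate list that contains both matching factors. If a model is meant to differ, say so and why. No rule for unmatched participants is needed.

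The cost is wording and one degree of freedom per model. Sex is already on the data collection form (Demographic Information). The Results section states that no statistical analyses have yet been run, so the change can still be prespecified.

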**Objective:**

This study aims to evaluate MIA in individuals who have undergone transradial amputation and use myoelectric prostheses, compare it with a healthy control group, and examine its association with upper extremity functionality and proprioception.

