### Demographic Information

Demographic data will be collected through face-to-face interviews using a standardized data collection form developed by the research team. The recorded variables will include age, sex, height, weight, BMI, educational level, occupation, year and cause of amputation, dominant side, side of amputation, duration of prosthesis use, current medication use, and history of previously used prosthetic systems. For individuals with transradial amputation, stump length will be measured using a tape measure as the distance from the olecranon to the most distal end of the residual limb.

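### The amputee-versus-control ANCOVA adjusts for residual limb length, which is measured only in amputees; under listwise deletion no controls remain

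*Protocol article*

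**What the plan says.** The objective is to measure motor imagery ability in amputees and "compare it with a healthy control group". Outcome Measures states that "the primary outcome is MIA assessed using the MIQ-3".

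Textbox 2 holds the analysis plan. Its Demographics entry sets the group coding: "Amputee (group 1) and control (group 2) demographics will be compared". Its entry on motor imagery variables begins "Measures will include the Movement Imagery Questionnaire-3, including its subscales: kinesthetic MI, internal MI, external MI, and total score", goes on to the Orientate and execution/imagery time measures, and then gives one rule for all of them: "Comparisons will be performed using the analysis of covariance, adjusting for age, dominance, and residual limb length". A nonparametric alternative is allowed if the ANCOVA assumptions fail. The entry on missing data says: "Missing data will undergo listwise deletion".

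Demographic Information says who has the covariate: "For individuals with transradial amputation, stump length will be measured using a tape measure". In Textbox 1 a residual limb length of 5 to 25 cm is a criterion for the amputee group; the control list has no counterpart.

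The two regression entries in Textbox 2 (function and proprioception) use the same three covariates and do not say which participants are included. For joint position sense, JPS Description gives another list: "Covariates such as age, sex, amputation level, prosthesis experience, and tested side will be recorded and adjusted for in the statistical analyses".

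**The concern.** A covariate in a between-group model has to exist in both groups. Residual limb length does not exist in a person with two intact arms, so its absence in controls is structural. The deletion rule has no exception for a variable that does not apply. Followed literally, the plan removes the comparison group from the only analysis that Textbox 2 specifies for the primary comparison.

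The analyst would then have to depart from the plan, either by dropping the covariate or by inventing a value for controls. Neither route is fixed in advance. They give different group estimates and different precision, and the choice would be made with the data in hand.

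**Working it through.** **Which comparison the ANCOVA serves.** The sentence does not name its groups. Three facts settle the reading: the objective requires amputee versus control, the Demographics entry defines those two groups, and comparisons within amputees have their own entry (Amputee-specific analyses). If the ANCOVA were amputee-only, Textbox 2 would contain no analysis of the primary objective.

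**The model as written.** The plan gives no figure for the adjusted model, so there is none to reproduce. Inputs: 15 per group (Participants); covariates age, dominance and limb length; limb length blank in controls.

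- Complete cases after listwise deletion: 30 − 15 = 15, made up of 15 amputees and 0 controls.
- Design columns: intercept, group, age, dominance, limb length = 5. Rank = 4, because group equals the intercept in every remaining row.
- The group effect is therefore not estimable.
- With limb length removed and age and dominance kept, there are 30 complete cases, 15 versus 15, and the group effect is estimable.

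**If controls are given a constant value c.** Leave age and dominance aside for simplicity. The slope b then comes from amputees alone, and

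- group estimate = (amputee mean outcome − control mean outcome) + b(c − L̄), where L̄ is the mean amputee limb length;
- variance ratio against the unadjusted comparison = 1 + [(c − L̄)²/Sxx] / (2/15), where Sxx is the amputees' sum of squares for limb length.

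Unless b is zero, the estimate moves with c. For the variance, the documents give only the 5 to 25 cm range. Assuming a uniform distribution over it, L̄ = 15, variance = 20²/12 = 33.3 and Sxx = 14 × 33.3 = 467.

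| Value given to controls | (c − L̄)² | Variance ratio |
|---|---|---|
| Amputee mean (same as centring, controls at 0) | 0 | 1.00 |
| 5 cm or 25 cm | 100 | 1 + 0.214/0.133 = 2.6 |
| 0 cm | 225 | 1 + 0.482/0.133 = 4.6 (standard error × 2.1) |

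Simulation of the 0 cm case gave a median of 4.56. The ratio also depends on the assumed spread: with mean 15 and SD 3, Sxx = 14 × 9 = 126 and the 0 cm ratio is 1 + 1.786/0.133 = 14.4.

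**With age and dominance in the model** (2,000 simulated covariate sets; age uniform 18 to 65, dominance 0/1, limb length uniform 5 to 25 cm, all assumed), mean variance inflation for group is:

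- no limb length: 1.08;
- centred on the amputee mean, controls at 0: 1.08;
- intact forearm length for controls (assumed mean 26 cm, SD 1.5): 3.2;
- controls at 0 cm: 5.4.

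**Covariate lists for proprioception.** Textbox 2 has age, dominance and residual limb length. JPS Description has age, sex, amputation level, prosthesis experience and tested side. Only age is plainly common to both. Amputation level cannot vary, because eligibility requires a transradial amputation, and prosthesis experience does not exist in controls.

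**The case against.** The strongest reply is that the model can be rescued without harm. Centre limb length on the amputee mean, set controls to 0, and the covariate is orthogonal to group: the variance ratio is 1.00 and the coefficient is the amputee-control difference at the average limb length. This is correct. It disposes of any claim that the model either cannot be run or must return a badly inflated standard error. It does not dispose of the defect, because the plan does not state this coding and other codings give other answers.

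It can also be said that losing every control assumes their cells are left blank. That is so, but blank is what the measurement rule produces, and no passage says otherwise. The nonparametric fallback does not help: it is triggered by failed ANCOVA assumptions, and an inapplicable covariate is not one of those.

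Several stronger readings are tempting and are not supported:

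- A reader might infer that the trial cannot answer its primary question. The independent-samples t test used for the sample size, or an ANCOVA without limb length, remains available from the planned data. What fails is this one specification.
- A reader might take a power of about 17% at d = 0.8 (against 56% for the unadjusted t test with 15 per group) as the plan's consequence. That figure belongs to raw 0 cm coding under an assumed uniform distribution, neither of which is in the documents; centring leaves 56%. That 56% falls short of the stated 80% is a separate matter.
- A reader might take the list in JPS Description as a rival covariate set for the MIQ-3. It stands in the joint position sense section, includes tested side and is worded as illustrative. Its conflict is with the proprioception entry of Textbox 2.
- A reader might call the two regression entries invalid. Restricted to amputees, limb length is a legitimate covariate there.
- Leaving sex out of the adjusted models is a choice, not an error; the groups are already matched on it.

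**Conclusion.** The point holds and should be corrected before analysis. As written, the ANCOVA for the motor imagery outcomes, the primary MIQ-3 among them, keeps 15 of 30 participants, no controls and no group contrast. This follows from the plan's own covariate list, measurement rule and deletion rule. It rests on two readings: that the ANCOVA is the amputee-versus-control comparison, and that controls have no recorded limb length.

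If controls are given a value instead, the size of the effect is not fixed by the documents. For a constant value between 0 cm and the amputee mean, under the uniform 5 to 25 cm assumption, the variance ratio runs from 4.6 down to 1.00, and the estimate shifts with the value chosen. The defect is this unstated choice; no single inflation or power figure can be attributed to the plan.

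The mismatch between the two covariate lists is a smaller, separate fault confined to proprioception, a secondary outcome.

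**What to change.** - Remove residual limb length from every amputee-versus-control model. Adjust those models only for variables defined in both groups: age, with sex as an option because it is the other matching variable, and dominance only if it has the same definition in amputees and controls.
- Use residual limb length and prosthesis experience in amputee-only models.
- In the Textbox 2 entries on function and proprioception, state that regressions using limb length are amputee-only, or drop the covariate there.
- Make the covariates in JPS Description and in the proprioception entry of Textbox 2 agree, and delete amputation level, since all amputees are transradial.

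The cost is a wording amendment. No new data are needed. The Results section reports 16 participants assessed and no statistical analysis yet conducted, so the change can be made and dated before any results are seen.
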